### Sampling and Detection

#### Urine Sampling and Storage

All enrolled participants will be provided with a sterile cup to collect no less than 5 milliliters of midstream urine at each visit. The sampled urine tubes will be frozen and stored at –20 °C no later than 4 hours after collection. Samples will be shipped frozen to a local laboratory for further analysis.

#### Urine Coding

At enrollment, each participant will be assigned a specific study number to protect their anonymity. The leading principal investigators will ensure that the participants’ anonymity is maintained in the trial database and during the whole research process. Samples collected from one participant at one time will be labeled with the same number to allow tracking and identification of any aliquot prepared from the original urine and for sample programming in laboratory analyzers. The test results will be held securely and separately from the eCRFs, ensuring that clinical decisions will not be influenced by the test results.

#### Laboratory Detection

Urine samples will be thawed at room temperature and centrifuged at 3000 rpm for 10 minutes. The supernatant will be used for detection.

Urine misfolded proteins will be detected by Pre-Eclampsia Detection Kit (CercaTest RED, Shuwen, China) since misfolded proteins can selectively bind to the Congo Red dye. When a mixture of the Congo Red and urine from a pregnant woman is loaded onto a chromatographic column mounted in a detection cuvette, the presence (positive) or absence (negative) of misfolded proteins can be determined based on the color of the eluent in the cuvette. The eluent will also be applied for quantitative measurement using the HACH DR1900 instrument by detecting the absorbance at a wavelength of 520-600 nanometers.

PlGF and sFLT-1 levels will be detected by the Elecsys PlGF and Elecsys sFlt-1 detection kits (Roche, Germany), respectively. The total urine protein/creatinine ratio will be detected by the Total Protein in Urine/CSF (TPUC) Kit and Creatinine Kit (Mindray, China), all according to the manufacturers’ instructions.

### Selection of Predictor Variables

According to the objective of this study, the misfolded protein level in urine will be considered as a predictor candidate for PE onset or adverse outcomes. Other preset variables include: (1) demographic factors, including high-risk factors of PE; (2) urine biomarkers reported in the literature; (3) medication; and (4) routine clinical variables or laboratory tests in daily practice (Textbox 2). The determination of valid variables will be based on the statistical analysis results with a significance level of *P*<.05.

Preset variable candidates for model development.Demographic factorsAgeBMIConception modeParityPreexisting hypertension, diabetes, autoimmune diseases (systemic lupus erythematosus, antiphospholipid syndrome)Urine biomarkersMisfolded proteinsPlacental growth factorSoluble FMS-like tyrosine kinase 1Total proteinCreatinineMedicationAspirinAntihypertensive drugsRoutine clinical variables or laboratory testsBlood pressureAspartate aminotransferaseLactate dehydrogenaseSerum creatinineProteinuria (spot urine protein, 24-hour urine protein)Uterine artery pulse index

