**Conclusions:**

Upon completion of the study, we expect to derive an accurate PE prediction model, which will allow for proactive management of pregnant women with clinical suspicion of PE and possibly reduce the associated adverse pregnancy outcomes. The additional prognostic value of misfolded proteins is also expected to be confirmed.

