### Sample Size

The target negative predictive value (NPV) is 99% and the target positive predictive value (PPV) is 54.0%. A positive test rate of 15% is assumed. The Type I error is set to .05. A sample size of 280 should be sufficient to detect NPV>90% and PPV>25% with 80% power. Therefore, at least 300 eligible participants will be included in this study considering a dropout rate of 6%. To avoid an overrepresentation of cases of late-onset PE, no more than 50% of the enrolled participants will be at 32 weeks gestation or above and no less than 20% of the enrolled participants will be at gestational week below 28+0 at inclusion.

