### Statistical Analysis

All variables will be compared between case and control groups. Either parametric or nonparametric tests will be applied for continuous variables and *χ*^2^ tests will be used for categorical variables. Receiver operating characteristic analysis will be used when applicable. Univariable or multivariable logistic regression will be applied to develop the prediction models. All *P* values will be two-tailed. The statistical analysis will be run on SPSS version 27 (IBM) statistical software.

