### Limitations

Although use of a prospective cohort in undiagnosed populations provides the best avenue for discovering predictive biomarkers, these markers or their combinations must be rigorously validated in internal/external cohorts to ensure their potential for PE prediction. The single-center nature of this study and prospective recruitment may imply the potential for selection bias. In addition, the enrollment was mainly conducted at prenatal clinics, and this might introduce selection bias regarding the severity of disease, as women with sudden onset of organ complications are more often seen at the emergency clinic. Therefore, future investigations with larger populations, along with assessment of the long-term outcomes of infants will be necessary to ensure the accuracy of the prediction model obtained in this trial and to establish the clinical utility of this tool for routine use in pregnancy care.

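### Choosing predictors by P<.05 from about 21 candidates, with about 25 PE events implied by the plan's own inputs, does not support the accurate combined model that the article expects

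*Protocol article*

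**What the plan says.** Selection of Predictor Variables in the protocol article refers to Textbox 2, which lists candidates under four headings: demographic factors, urine biomarkers (misfolded proteins among them), medication, and routine clinical or laboratory variables. The rule for choosing among them is: "The determination of valid variables will be based on the statistical analysis results with a significance level of" P<.05. It does not say whether the P value comes from one-at-a-time tests or from a joint model. Statistical Analysis adds: "Univariable or multivariable logistic regression will be applied to develop the prediction models".

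Sample Size deals only with the single test: "The target negative predictive value (NPV) is 99% and the target positive predictive value (PPV) is 54.0" per cent, and "A positive test rate of 15% is assumed". It gives no PE event rate and no sample-size reasoning for the model.

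On what the model will deliver, the Abstract's Conclusions say "we expect to derive an accurate PE prediction model" once the study is complete. Limitations is more guarded: "these markers or their combinations must be rigorously validated in internal/external cohorts". It leaves confirmation of the model's accuracy to later, larger studies. The model is a secondary objective.

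**The concern.** When candidates are many relative to events, a significance filter does two things. It keeps variables whose effects look large by chance in this sample, so the fitted model appears to discriminate better than it will elsewhere and its predicted risks are too extreme. It also discards real predictors of moderate strength that happen to miss the threshold. The study's own marker is one of the candidates exposed to this.

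The stake is the second half of the secondary objectives. The article hopes the model will guide management of women with suspected PE. A model with a calibration slope well below 1 overstates risk in women it ranks high and understates it in women it ranks low.

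**Working it through.** **1. The plan's own sample size.** Inputs from Sample Size: NPV 0.99 against 0.90, PPV 0.54 against 0.25, 15% test-positive, 80% power, N = 280, and "The Type I error is set to .05". Sidedness is not given there; Statistical Analysis says P "values will be two-tailed".
- With 280 women, 0.15 × 280 = 42 test positive and 238 test negative.
- One-sample binomial calculations for PPV, the limiting comparison, need N of about 92 to 123 one-sided or 117 to 155 two-sided for 80% power.
- Exact joint power for both comparisons at N = 280 is 0.98 (one-sided .05) or 0.96 (.025 per tail).
- Dropout: 280 / 0.94 = 298, consistent with 300.

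So 280 is not reproduced as the N for 80% power under the one-sample variants, but it is sufficient for the single test, as the text claims. None of this concerns the model.

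**2. Candidates (Textbox 2).** Demographic 7 + urine 5 + medication 2 + routine 7 = 21, with spot and 24-hour protein counted separately. With proteinuria counted once the total is 20, and 18 if the preexisting conditions also form one composite. It is 23 if the two autoimmune diseases, and systolic and diastolic pressure, are split.

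**3. Events implied by the plan's inputs.** PE rate = 0.15 × 0.54 + 0.85 × (1 − 0.99) = 0.081 + 0.0085 = 8.95%.
- Events = 0.0895 × 280 = 25.1 (26.9 of 300).
- Events per candidate = 25.1 / 21 = 1.2 (1.1 for 23 candidates, 1.4 for 18).

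**4. If incidence is higher.** The rate above is derived, not stated. The targets carry no time window, while cases are counted to 42 days postpartum.

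| PE incidence | Events of 280 | Per candidate (21) |
|---|---|---|
| 8.95% (plan's inputs) | 25 | 1.2 |
| 12.25% (NPV and PPV at their null bounds) | 34 | 1.6 |
| 20% (assumed) | 56 | 2.7 |
| 40% (assumed) | 112 | 5.3 |

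**5. Sample size for a 21-parameter model.** The criteria used are expected shrinkage of at least 0.90 and Nagelkerke R² optimism of at most 0.05. The shrinkage criterion is N = p / [(S − 1) ln(1 − R²/S)], with R² on the Cox–Snell scale. At 8.95% incidence the maximum Cox–Snell R² is 0.453. For an assumed Nagelkerke R² of 0.15, R² = 0.15 × 0.453 = 0.068 and N is about 2,677.
- At Nagelkerke R² of 0.15 / 0.30 / 0.50, the larger of the two criteria gives about 2,677 / 1,284 / 807.
- Expected shrinkage at N = 280 is 0.49 / 0.67 / 0.78.
- N = 280 supports roughly 2, 4 to 5, or 7 candidate parameters.
- At 20% to 40% incidence the requirement is 443 to 1,886, still above 280.

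**6. Simulating the stated rule.** Set-up: 280 women, 21 or 22 independent normal candidates, each screened at P<.05 on its own (an assumed reading of the rule), survivors entered in ordinary logistic regression, performance judged in new data. Effects are assumed: either three real predictors with log-odds 0.7, 0.5 and 0.4 per SD, or five real predictors in two effect sets.

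| Incidence | Effects | Apparent AUC | AUC in new data | Slope |
|---|---|---|---|---|
| 8.95% | three real | 0.77 | 0.67 to 0.69 | 0.60 to 0.67 |
| 8.95% | five real, set 1 | 0.81 | 0.74 | 0.70 |
| 8.95% | five real, set 2 | 0.87 | 0.81 | 0.75 |
| 20% | three real | 0.75 | 0.71 | about 0.8 |
| 40% | three real | 0.74 | 0.71 | 0.83 to 0.85 |

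At 40% the five-predictor sets give optimism of 0.02 to 0.03 and slopes of 0.84 to 0.89. At 8.95% the real predictor with log-odds 0.4 per SD (odds ratio exp(0.4) = 1.49) was dropped in 54% to 57% of simulated trials.

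**The case against.** The strongest reply has four parts.

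First, the 25 events are back-calculated from performance targets, and a cohort with suspected PE followed to 42 days postpartum may yield more. This stands, and it is why the result is given as a range. It weakens the size of the problem but does not remove it: events per candidate stay at 5.3 or below over the range considered.

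Second, a reader might infer that no optimism correction and no test of added value will be done. The article does not say that. It is a condensed text, a fuller protocol or analysis plan may contain both, and Limitations names validation as a requirement. That silence is not relied on. The point rests on what is written: the selection rule, the candidate list, a sample size that addresses only the single test, and the expectation of an accurate model. A bootstrap elsewhere would measure the optimism but would not change the rule.

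Third, a reader might infer that evaluation of misfolded protein depends on surviving the filter, or that the sFLT-1/PlGF ratio is ruled out because the two are listed separately. Neither is supported. The marker is also to be assessed on its own. Textbox 2 appears to list analytes: it lists urine protein and creatinine separately too, although Laboratory Detection says their ratio will be measured.

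Fourth, the simulated effects and the independence of candidates are assumptions, and some candidates plainly overlap. This also stands. Scenarios with no real predictors, or with every candidate entered, would look worse, but they do not describe this plan and carry no weight here.

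**Conclusion.** The concern holds in limited form. Under the plan's own inputs there are about 1.2 events per candidate. Applying the stated rule would then overstate the AUC by about 0.08 (0.06 to 0.10 across the effect sets tried), with a calibration slope of about 0.6 to 0.75. At an assumed 20% to 40% incidence the optimism falls to about 0.02 to 0.04 and the slope rises to about 0.8 to 0.9. These figures assume univariable screening, independent candidates and the effect sizes shown.

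The tempting stronger reading, that the model is bound to be badly overfitted and the secondary objective cannot be met, goes too far. Severe overfitting follows only if events are near 25, and the document does not fix that number. What can be said is that the stated rule does not support the word accurate in the Abstract, and that it can discard a moderate real predictor, possibly misfolded protein itself, from the combined model. Because the model is secondary and the NPV/PPV assessment does not pass through the filter, this is something that should be fixed rather than a defect in the primary analysis.

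**What to change.** - Replace the P<.05 filter with a small core model prespecified without reference to the outcome data: about 3 to 5 terms, fewer if events turn out near 25. Force misfolded protein in and draw the other terms from Textbox 2. Gestational age, known for every woman at enrolment, is a sensible candidate but would be an addition to that list and should be declared as such.
- Fit the model by Firth or ridge penalised logistic regression.
- Report bootstrap optimism-corrected AUC and calibration slope, repeating any selection step within each resample.
- Assess the added value of misfolded protein by comparing the core model with and without it. Use a penalised likelihood-ratio test under Firth, or an ordinary one on an unpenalised fit of the small model; the ordinary test does not carry over to a ridge fit.
- Label selection from the full candidate list exploratory, and describe the result as a developed model that needs external validation rather than as accurate.

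The cost is revised wording, and R or an SPSS extension alongside SPSS 27. No extra participants or measurements are needed, and the article states that analysis had not begun. The downside is a less flattering reported AUC.

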### Recruitment

Potential participants will be identified by the research team from the antenatal clinic at Women’s Hospital, School of Medicine, Zhejiang University. Eligible women must meet all inclusion criteria without violating any of the exclusion criteria (Textbox 1) and will be provided with the participant information and consent form to sign. A research team member will provide a verbal explanation of the trial, including a description of the trial processes, the voluntary nature of the trial, and that a decision of whether or not to participate will not affect normal clinical care. No trial-related procedures will be performed on any individual without their prior written informed consent. All participants will be followed up until 42 days postpartum.

Inclusion and exclusion criteria for determining trial eligibility.Inclusion criteriaAged ≥18 years.Gestational week 20+0 to 33+6.Signed written informed consent.Single pregnancy.Clinically suspected preeclampsia (PE), meeting one or more of the following criteria:(i) new onset of elevated blood pressure (systolic ≥130 mmHg and/or diastolic ≥80 mmHg);(ii) aggravation of preexisting hypertension (increase of more than 30 mmHg systolic/15 mmHg diastolic from the basic blood pressure in patients without hypertension, or a significant increasing trend or increase beyond the controlled level based on the original treatment for patients with hypertension);(iii) new onset of proteinuria (no urinary tract infection);(iv) one or more clinical symptoms indicate suspected PE (other possible causes have been ruled out): upper abdominal pain, headache with impaired vision, fetal growth restriction, thrombocytopenia (platelets count<100×10^9^/L), liver function impairment (elevated blood concentrations of liver transaminases up to twice the normal concentration), and renal impairment (serum creatinine>1.1 mg/dL or a doubling of the serum creatinine concentration in the absence of other renal disease).Exclusion criteriaConfirmed diagnosis of PE/chronic hypertension with PE (superimposed PE).Confirmed diagnosis of eclampsia.Confirmed diagnosis of hemolysis with a microangiopathic blood smear, elevated liver enzymes, and low platelets (HELLP syndrome).Fetal chromosomal abnormalities.Concomitant participation in another clinical study.Received investigational intervention drugs in the past 3 months.Visible hematuria.Preexisting renal disease.

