### Study Groups: Classification of Cases and Controls

Standard diagnostic criteria [24,25] for PE are new onset of hypertension (systolic blood pressure≥140 mmHg or diastolic blood pressure≥90 mmHg measured on two occasions at least 4 hours apart) and new-onset proteinuria (≥300 mg/day or protein/creatinine ratio ≥0.3 mg/dL) after 20 weeks of gestation. Diagnostic criteria in the absence of proteinuria include any of the following: (1) thrombocytopenia (platelets count<100×10^9^/L); (2) liver function impairment (elevated blood concentrations of liver transaminases to twice the normal concentration); (3) renal insufficiency (serum creatinine>1.1 mg/dL or a doubling of the serum creatinine concentration in the absence of other renal disease); (4) pulmonary edema; and (5) central nervous system abnormalities or visual disturbances.

Cases are defined as patients who develop PE at any time between the first visit to 6 weeks (42 days) postpartum.

Controls are patients who do not develop PE throughout the pregnancy and up to 6 weeks (42 days) postpartum.

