### Data Collection

Participant data for this study will be collected by investigators and input into an electronic case report form (eCRF). The data will be verified by the principal investigator when suspicious data entries are noted. The data manager will check the completion of the data for final analysis. The study will include 6 visits plus a postpartum documentation. The first visit starts at enrollment, followed by 4 visits once a week when participants come for their routine prenatal examinations. There will be one visit at delivery as well as one postpartum documentation. On occurrence of pregnancy complications, further visits are possible. The clinical data to be collected during each visit are summarized in Table 1. The time interval between two consecutive visits could be 7±2 days, and adherence to the time schedule is crucial for incorporating participant data into the final analysis.

**Table 1 table1:** Summary of the data collection procedure and timeline.

Data collected	Visit 1	Visit 2	Visit 3	Visit 4	Visit 5	Delivery	Postpartum	Unscheduled visit
Inclusion/exclusion criteria	✓							
Informed consent	✓							
General baseline feature	✓							
Chronic history	✓							
Pregnancy history	✓							
Concomitant medication	✓	✓	✓	✓	✓	✓	✓	✓
BMI	✓	✓	✓	✓	✓			✓
Blood pressure	✓	✓	✓	✓	✓		✓	✓
Sampling and detection	✓	✓	✓	✓	✓			✓
Preeclampsia assessment	✓	✓	✓	✓	✓	✓	✓	✓
Laboratory parameters (blood and urine)	✓	✓	✓	✓	✓			✓
Sonographic data	✓	✓	✓	✓	✓			✓
Delivery outcome						✓		
Pregnant woman status						✓	✓	
Fetal/neonatal status						✓	✓	

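### The preset predictor list leaves out gestational age, although entry spans 20+0 to 33+6 and case status is counted over follow-up of very unequal length

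*Protocol article*

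**What the plan says.** All references are to the protocol article.

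- **Selection of Predictor Variables, Textbox 2.** The candidates are described as preset and itemised in four blocks. The demographic block opens "Preset variable candidates for model development.Demographic factorsAgeBMIConception modeParityPreexisting hypertension, diabetes, autoimmune diseases". The other blocks are urine biomarkers, medication (aspirin, antihypertensives) and routine variables (blood pressure, AST, LDH, serum creatinine, proteinuria, uterine artery index). Variables are retained on the basis of P<.05. Gestational age is not listed.
- **Recruitment, Textbox 1.** Eligibility is "Gestational week 20+0 to 33+6".
- **Sample Size.** Enrolment is limited on gestational age in two ways. Entry at 32 weeks or later is capped at half of the cohort. For early entry there is a floor: "no less than 20% of the enrolled participants will be at gestational week below 28+0 at inclusion". The reason given for both limits is "To avoid an overrepresentation of cases of late-onset PE".
- **Study Groups.** "Cases are defined as patients who develop PE at any time between the first visit to 6 weeks (42 days) postpartum".
- **Statistical Analysis.** Cases and controls are compared on all variables, and "Univariable or multivariable logistic regression will be applied to develop the prediction models".
- **Data Collection.** "The first visit starts at enrollment, followed by 4 visits once a week".

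**The concern.** The design treats gestational age as important enough to set enrolment limits on it, but the model-building list has no place for it. Two consequences follow if the list is applied as written.

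First, the outcome has no fixed horizon from sampling. A woman who enters early is observed for longer than one who enters late, and a logistic model treats both as the same kind of observation unless gestational age (or follow-up time) is a covariate. Part of the spread in risk between women is then left unexplained, and predicted risks may be too high at one end of the entry range and too low at the other.

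Second, if misfolded-protein level also varies with gestational age, its association with preeclampsia is confounded by a variable that the listed models cannot adjust for. The same holds for the other urine markers and for any claim that one adds to another. The article does not say whether the marker varies with gestational age, so this is a possibility to guard against, not a demonstrated bias.

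**Working it through.** **Plan's own figure.** The article gives no figure for follow-up time by entry week, so there is none to reproduce. The sample-size figures are used only for the expected number of cases. The dropout step is consistent: 280/0.94 = 298, stated as at least 300.

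**Inputs.** Entry at 20+0 = 140 days and at 33+6 = 237 days (Textbox 1). Case window ends 42 days postpartum (Study Groups). Delivery week is not given; 37, 39 and 40 weeks (259, 273 and 280 days) are assumed.

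**Length of the case window.** Window = delivery day − entry day + 42.

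| Assumed delivery | Entry 20+0 | Entry 33+6 | Ratio |
|---|---|---|---|
| 40+0 | 280 − 140 + 42 = 182 d | 280 − 237 + 42 = 85 d | 2.1 |
| 39+0 | 273 − 140 + 42 = 175 d | 273 − 237 + 42 = 78 d | 2.2 |
| 37+0 | 259 − 140 + 42 = 161 d | 259 − 237 + 42 = 64 d | 2.5 |

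Counting only time before delivery, the ratio at 40+0 is 140/43 = 3.3. That is not the window the article uses to define a case.

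**Sampling range.** Four further weekly samples add 28 days nominally, so samples run from 20+0 to about 37+6. Gestational age at sampling is therefore the relevant covariate, not only gestational age at entry.

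**Expected cases.** From the planning values (15% positive, PPV 54%, NPV 99%): 0.15 × 0.54 + 0.85 × 0.01 = 0.0895, and 280 × 0.0895 = 25 cases. The same values imply sensitivity 0.081/0.0895 = 90.5% and specificity 0.8415/0.9105 = 92.4%.

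**Illustration of scale.** Assume a constant hazard, delivery at 39 weeks, a 20/30/50% mix entering at 24/30/33 weeks, and fixed sensitivity and specificity as above. The windows are 21, 15 and 12 weeks. The weekly hazard that gives 8.95% overall is 0.0064, and risk = 1 − exp(−0.0064 × weeks):

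| Entry week | PE risk | PPV | NPV |
|---|---|---|---|
| 24 | 12.6% | 63% | 98.5% |
| 30 | 9.1% | 55% | 99.0% |
| 33 | 7.4% | 49% | 99.2% |

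Under these assumptions, follow-up length alone moves risk from 7.4% to 12.6% with test accuracy unchanged. The hazard shape and entry mix are not in the article, and another hazard could shrink or reverse the gradient.

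**Precision by stratum.** At the 20% floor, 0.20 × 300 = 60 women enter below 28+0, and 60 × 0.15 = 9 test positive. A PPV of 5/9 has an exact 95% interval of 21% to 86%.

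**The case against.** The strongest reply is that the time-at-risk argument is borrowed from another weakness. The Objective section asks for short-term prediction, while the case definition has no horizon. With a fixed short horizon, follow-up would be nearly equal across women and the mechanism above would largely disappear. That is fair, and adding gestational age does not replace a horizon. But the article sets no horizon, so the mechanism applies to the plan as published.

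A second reply is that an unseen analysis plan may add the variable. The article, however, presents its list as preset and itemises it down to LDH and conception mode. Adding gestational age would depart from that list.

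A third reply is that cases are already few. Counting the pre-existing diseases as three, Textbox 2 holds 7 + 5 + 2 + 6 = 20 candidates for about 25 cases. This stands, and it argues for a single linear term and no more.

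A reader might also infer several stronger points, which the article does not support:

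- That the enrolment limits were set because of time at risk. The stated reason is late-onset disease.
- That the range in follow-up, or incidence under a constant hazard, is threefold. Over the article's own case window it is about twofold.
- That predictive values will be reported only pooled and will reflect a quota mix unlike the clinic's. The article gives planning targets only, leaves stratified reporting open, and does not show that either limit binds.
- That the whole analysis is unadjusted. Multivariable logistic regression is specified; what is missing is this covariate.

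**Conclusion.** The point holds in a limited form. The preset list omits a variable that the design itself controls and that determines how long each woman can become a case. The length of the case window differs about 2.1-fold across the entry range if delivery is at 40+0, and 2.1- to 2.5-fold for delivery at 40 to 37 weeks. The consequences are possible confounding of the misfolded-protein association and poorer calibration. Neither its direction nor its size can be fixed from the article, because it gives no hazard, no entry mix and no relation between the marker and gestational age.

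It would go too far to say that a model without gestational age cannot give a valid risk: such a risk is conditional on the predictors that are in the model, and omission costs discrimination, calibration and transportability. Nor does the omission overturn the primary comparison. In the illustration PPV (49% to 63%) and NPV (98.5% to 99.2%) stay well above the planning thresholds of 25% and 90%. This should be corrected, but it does not threaten the data or the enrolment.

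**What to change.** Add gestational age at sampling to Textbox 2 as a continuous variable. State that it is forced into the multivariable prediction models and into the adjusted misfolded-protein analysis, regardless of the P<.05 selection rule.

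No new data should be needed: gestational age must already be known for eligibility and the enrolment limits, and sampling dates follow from the visit schedule. According to the Results section, analysis starts only after follow-up is complete, so the change could still be prespecified when the article was written. The statistical cost is one degree of freedom against roughly 25 expected cases. A spline would cost more and is hard to justify with so few cases.

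NPV and PPV by gestational-age stratum may be shown descriptively with confidence intervals. This is optional, and the stratum below 28+0 may have only about 9 positive tests.
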